### Study design, treatments, and blinding

The ISTRA ADJUST PD study is a multicenter, randomized, open-label, parallel-group controlled study (Fig. 1). Study participants will be randomly assigned to either the istradefylline group or the control group in a 1:1 ratio. Randomization will be centrally performed via computer allocation, using a minimization method and stratified according to age (< 60 or ≥ 60 years), levodopa equivalent dose (< 400 or ≥ 400 mg/day), and dyskinesia (presence or absence). The study will be conducted from February 2019 to February 2022 (with the registration period lasting until November 2020), and the expected duration of involvement for each participant is 37 weeks. The observation schedule is shown in Table 1; most observations will be conducted at 4- or 12-weekly intervals during the study period.

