The criteria for the titration of levodopa-containing medications are as follows: if the clinical global impression of severity scale (CGI-S) is ≥ 4 on the day of observation, the dose is incrementally increased by 50 mg/day. If an intolerable adverse reaction occurs due to the dose increase, reduction of the dose of the levodopa-containing medication is allowed (at the physician’s discretion; no reduction amount is specified). For levodopa, only a dose increase of 50 mg/day per visit will be allowed.

Once-daily oral administration of a 20 mg istradefylline tablet will be started at Week 0. At Week 1, if the treatment is well tolerated and motor symptoms persist, the dosage of istradefylline will be increased to 40 mg, once daily. Dose reduction is allowed if treatment is not tolerable.

Changes in the dosage and dosing regimen of anti-PD drugs are not permitted within 4 weeks before enrollment and during the treatment period. However, dose reduction of a specific drug is permitted, if intolerable adverse reactions causally associated with that drug appear.

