### Efficacy outcomes

The primary study endpoint is the comparison of the cumulative additional dose of levodopa-containing medications during the treatment period (from Week 0 to Week 37) between patients with PD who receive adjunctive istradefylline and those who do not.

Secondary efficacy endpoints are the between-group comparisons of additional levodopa doses on each observation day from Week 4 to Week 36; the number of days until the first dose increase after Week 4; change in dose of levodopa-containing medications until Week 36; CGI-S score and change in score; CGI-improvement scale (CGI-I) score (to measure the degree of improvement from the previous evaluation); patient global impression of severity (PGI-S) score and change in score; PGI-improvement (PGI-I) score (to measure the degree of improvement from the previous evaluation); mH&Y staging scale (ON/OFF) score and change in score; MDS-UPDRS part I score (nonmotor experiences of daily living), part II score (motor experiences of daily living), part III score (motor examination), part IV score (motor complications), and change in scores; Parkinson’s Disease Questionnaire-39 (PDQ-39) score and change in score; and correlations between any of the score changes. Correlations between CGI-S and other measures (e.g., MDS-UPDRS3, MDS-UPDRS4, and PGI-S) will be evaluated to confirm whether dose escalation decisions would differ between using CGI-S and using other measures.

Patients will also wear a wristband-type triaxial accelerometry system (UW-301BT, Hitachi Systems Ltd., Tokyo, Japan) on their non-dominant wrist for 7 days every 3 months during the study; data extracted from the wearable device will include movement frequency and intensity, gait (step count, pace, and laterality), and sleep (bedtime, awakening time, duration of sleep, sleep efficiency, sleep onset latency, movement during sleep, and number of episodes of getting out of bed).

Safety endpoints for this study will include adverse events and adverse drug reactions classified based on System Organ Class and Preferred Term defined in the Medical Dictionary for Regulatory Activities (Japan edition), using the most recent version at the time of coding.

Exploratory endpoints include evaluation of the correlation between the information extracted from the wearable device and the primary/secondary efficacy endpoints.

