### Statistical methods

There have been no previous studies investigating the effect of istradefylline treatment on the flexibility of the doses of levodopa-containing formulations. Thus, we used real-world data based on information from the medical claims database (Medical Data Vision Co., Ltd., Tokyo, Japan) to estimate the between-group difference in the Mann–Whitney U test by simulating cumulative L-DOPA doses in PD patients (non-istradefylline treatment), which would ensure a power of 80% with groups of 50 patients. In this condition, an approximate 21.3% in between-group difference over a period of 9 months (270 days) is detectable as the area under the curve (AUC) of cumulative additional L-DOPA doses between treatments (data on file; Kyowa Kirin Co., Ltd., Tokyo, Japan). Based on the mean additional levodopa dose over 9 months (approximately 265 mg) in a previously published study [36], recommendation from the Expert Medical Advisory board for this study, and the clinical experience in Japan, we anticipated that istradefylline might suppress the dose increase of levodopa-containing medications by 20%. Therefore, the sample size was set at 111 patients, to allow for 10% drop-outs and to ensure that there were 50 patients per group with data evaluable for the efficacy analyses.

The efficacy and safety analysis sets will include all patients who meet the inclusion criteria and do not meet the exclusion criteria, with the exception of those who withdraw consent before the start of the observation period (Week 0) or are withdrawn by the study investigator, and those randomly assigned to istradefylline treatment but who do not start administration of istradefylline. The patient background data that will be collected will include date of birth (if not disclosed, age at the date of consent), sex, height, weight, caregiver availability, pregnancy, hospitalization, year of onset of PD, year of onset of wearing-off, family history of PD, year of initial treatment with levodopa, daily dose and number of administrations of levodopa, levodopa equivalent dose, MMSE score, and mH&Y (ON/OFF).

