Summary statistics will be calculated for quantitative variables, and the number of patients and percentage will be determined for categorical variables. For the primary endpoint, the cumulative additional levodopa dose (AUC during the treatment period) will be calculated using the Mann–Whitney U test. The cumulative additional dose (AUC of additional dose during the treatment period) will be calculated as the total dose (daily dose × number of days) added to the dose of levodopa-containing medications (300–400 mg/day) at randomization. For the secondary endpoints, the cumulative additional doses of levodopa will be calculated for the patients who completed the treatment (Week 37). A log-rank test will be performed on the number of days from the start of observation (Week 0) to the time of dose increase, and time-to-event curves will be created using the Kaplan–Meier method. Summary statistics of the secondary endpoints at each observation time point will be calculated for each group, and mean and standard deviation data will be plotted in a line graph. Scores at each time point will be compared between groups using the Mann–Whitney U test. Correlation of the secondary endpoint scores will be performed using the Spearman correlation coefficient, and scatter plots will be created. A two-sided significance level of 5% will be applied to between-group comparisons, and two-sided 95% confidence intervals will be calculated. No imputation will be made for missing data. We will prepare a detailed statistical analysis plan before the database is finalized and locked. Statistical analyses will be conducted using SAS version 9.4 (SAS Institute Inc., Cary, NC, USA).

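### The unadjusted Mann–Whitney primary test is valid, but it leaves out the three minimisation factors and Week-0 CGI-S and so probably gives up precision

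*Protocol article*

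**What the plan says.** Under Statistical methods, the primary endpoint is the AUC of additional levodopa dose, and the test is named without any stratum or covariate: "the cumulative additional levodopa dose (AUC during the treatment period) will be calculated using the Mann–Whitney U test". The sample size was simulated for this same test, at a between-group difference "which would ensure a power of 80% with groups of 50 patients". The level is also fixed: "A two-sided significance level of 5% will be applied to between-group comparisons". A detailed SAP is promised before the database is locked.

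Under Study design, treatments, and blinding, patients are "randomly assigned to either the istradefylline group or the control group in a 1:1 ratio", "using a minimization method and stratified according to age" (cut at 60 years), levodopa equivalent dose (cut at 400 mg/day) and presence of dyskinesia. The titration rule in the same section says that if CGI-S is 4 or more "on the day of observation, the dose is incrementally increased by 50 mg/day".

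Table 1 schedules CGI-S at Week 0 and at every four-weekly visit from Week 4. The first decision on a levodopa increase is at Week 4. Efficacy outcomes lists "CGI-S score and change in score" among the secondary endpoints.

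**The concern.** The design treats three baseline factors as important enough to balance, and the stated analysis then drops them. If those factors predict the outcome, an analysis that ignores them carries between-patient variation that the allocation has already evened out across arms. Its standard error is then larger than it need be.

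The stronger candidate is CGI-S. The outcome accumulates how early and how often CGI-S reaches 4 after treatment starts, so a patient's pre-treatment CGI-S should carry information about it. CGI-S is not a minimisation factor, so neither the allocation nor the primary test takes account of it.

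Power is at stake in a trial with little to spare: Statistical methods gives 80% power at a 21.3% difference but anticipates 20%.

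**Working it through.** **Inputs from the protocol article (Statistical methods).** 50 evaluable patients per group; two-sided 5% level; 80% power at a 21.3% difference in AUC; anticipated effect 20%; 10% dropout; 111 patients in total.

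**Inputs not given.** The SD of the AUC (the claims-database simulation is data on file) and the share of variance explained by the covariates (R²). R² is therefore an assumption, shown as a range.

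**Step 1: the plan's own figure.** 100 / 0.90 = 111.1, which is 112 if rounded up, against 111 stated. This is reproduced to within one patient.

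**Step 2: calibration.** The 80% statement cannot be recomputed without the SD, but it fixes the scale. At a 21.3% difference the expected test statistic is 1.96 + 0.84 = 2.80. With 50 per group the standardised effect is 2.80 × √(2/50) = 0.560, so the implied SD is 21.3 / 0.560 ≈ 38% of the control mean. Allowing for the efficiency of the Mann–Whitney test under normality (0.955) gives about 37% and leaves the power figures below unchanged.

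**Step 3: unadjusted power at 20%.** Φ(2.80 × 20/21.3 − 1.96) = Φ(0.67) ≈ 75%.

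**Step 4: with adjustment.** Covariates that explain a share R² of the variance reduce the SD by √(1 − R²):

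power = Φ(2.80 × (20/21.3) / √(1 − R²) − 1.96)

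| R² (assumed) | Power at 20% | Detectable at 80% power, 21.3 × √(1 − R²) | Unadjusted patients that 100 adjusted ones are worth, 100/(1 − R²) |
|---|---|---|---|
| 0 | 74.9% | 21.3% | 100 |
| 0.05 | 77.0% | 20.8% | 105 |
| 0.10 | 79.2% | 20.2% | 111 |
| 0.15 | 81.4% | 19.6% | 118 |
| 0.20 | 83.7% | 19.1% | 125 |
| 0.30 | 88.2% | 17.8% | 143 |

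The R² at which power at 20% reaches 80% is 1 − (20/21.3)² = 0.118, or about 12%.

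**Step 5: which covariates matter.** An illustrative simulation used 100 patients, minimisation on three binary factors, the CGI-S ≥ 4 rule and 1,500 runs per scenario. All severity parameters were assumed.

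| Covariate R² in the scenario | AUC reduction | Mann–Whitney | Rank ANCOVA, three factors | Rank ANCOVA, factors + Week-0 CGI-S |
|---|---|---|---|---|
| 0.30 | 25% | 75.8% | 78.4% | 85.5% |
| 0.41 | 23% | 55.9% | 57.3% | 75.1% |

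Here the factors alone added 1.4 to 2.6 points, and Week-0 CGI-S supplied most of the gain. That split depends on the assumed strengths: dyskinesia and levodopa equivalent dose were given modest effects and age none.

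With no treatment effect, across these two settings and a third with R² 0.63, the Mann–Whitney test rejected in 3.5% to 5.7% of runs and the fully adjusted rank ANCOVA in 4.4% to 5.7%. Neither range suggests a material loss of error control.

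**The case against.** The best defence is that nothing here is an error. The Mann–Whitney test is a legitimate comparison of randomised groups, the sample size was simulated for that test, and its error rate already allows for chance imbalance in any baseline variable. All of this stands. A reader might infer that minimisation without adjustment invalidates the test or makes it conservative. The documents do not support the first, and the second holds only to the extent that the minimisation factors are prognostic, which they do not show.

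A second defence is that adjusted analyses belong in the SAP. That covers supplementary analyses. It does not cover the choice of primary test, which this article makes and ties to the sample size.

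A third defence concerns CGI-S. A reader might take the outcome to be almost determined by CGI-S and carry that over to the Week-0 score. Week-0 CGI-S triggers no increase, because decisions start at Week 4. It helps only through its correlation with later scores, which the documents do not report. Discretionary levodopa reductions for intolerable reactions loosen the link, and the eligibility limits on stage and levodopa dose may narrow the spread of severity. Nor is the baseline score unused in the trial, since the secondary change in CGI-S needs it. It is absent only from the primary test.

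Finally, the 75% figure comes from the gap between 20% and 21.3%, not from omitting covariates. Adjustment could offset that gap but did not cause it.

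**Conclusion.** The point holds as one of efficiency. The stated primary test is valid, but it ignores baseline information that the trial uses for allocation or already collects, and it probably loses precision by doing so, chiefly by omitting Week-0 CGI-S.

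The direction is well supported. The size is not known: power at the anticipated effect would rise from about 75% to between 77% and 88% for R² between 0.05 and 0.30. A reader might conclude that adjustment is sure to restore 80% power. It does so only if R² is about 0.12 or more, and no figure in the documents establishes that.

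The range rests on a normal location-shift approximation applied to an outcome built from 50 mg steps, and on a claims-database simulation that is not shown.

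**What to change.** Before database lock, prespecify a single primary model in the SAP: a rank ANCOVA of AUC on arm, age group, levodopa-equivalent-dose group, dyskinesia and Week-0 CGI-S. Istradefylline starts at Week 0, so state that only the pre-treatment CGI-S rating is used. Later ratings are made open-label and may be affected by treatment, so they must not enter the model. Because the plan excludes imputation, also state how a patient without a Week-0 score is handled.

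Keep the unadjusted Mann–Whitney test as a sensitivity analysis.

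Separately, report a covariate-adjusted mean difference in AUC, in mg, with a bootstrap 95% CI as a supporting estimate. Neither the Mann–Whitney test nor the rank ANCOVA estimates the percentage difference in AUC on which the trial was planned.

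The cost is SAP wording and a little programming. It needs no additional patients, visits or data items.

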**Fig. 1 Fig1:**
[figure not shown]
ISTRA ADJUST PD study design. W, week

**Table 1 Tab1:** Observation schedule

	Date of consent or enrollment	Observation period (week)											
		0	1^a^	4	8	12	16	20	24	28	32	36^b^	37^c^
Informed consent	●												
Eligibility confirmation	●	●											
MMSE	●												
Patient background	●												
Medical history/complications		●											
Decision on dose increase of levodopa-containing medications				●	●	●	●	●	●	●	●	●	
CGI-S		●		●	●	●	●	●	●	●	●	●	
CGI-I				●	●	●	●	●	●	●	●	●	
PGI-S		●		●	●	●	●	●	●	●	●	●	
PGI-I				●	●	●	●	●	●	●	●	●	
mH&Y (ON/OFF)		●				●			●			●	
MDS-UPDRS (part I, II, III, IV)		●				●			●			●	
PDQ-39		●				●			●			●	
Wearable device data	●					●			●			●^e^	
Symptom diary^d^	●					●			●			●^e^	
Hospitalizations	●	●	●	●	●	●	●	●	●	●	●	●	●
Concomitant medication check	●	●	●	●	●	●	●	●	●	●	●	●	●
Adverse events	●	●	●	●	●	●	●	●	●	●	●	●	●
Information on discontinuation		At any time											
Data entry into the case report form		Within 2 weeks after each visit											

*CGI-I* clinical global impressions of improvement, *CGI-S* clinical global impressions of severity, *MDS-UPDRS* Movement Disorder Society Unified Parkinson’s Disease Rating Scale, *mH&Y* modified Hoehn & Yahr scale, *MMSE* Mini-Mental State Examination, *PDQ* Parkinson’s disease questionnaire, *PGI-I *patient global impressions of improvement, *PGI-S* patient global impressions of severity

^a^Istradefylline group only

^b^Or the day immediately after discontinuation

^c^Not a mandated visit if judged to be unnecessary

^d^Symptoms will be recorded in symptom diaries by study participants or their family members/caregivers. The investigator, subinvestigator, or study cooperator are also allowed to record symptoms in the diary during the visit, or in the case that the patients are hospitalized. Visits will be conducted in an outpatient setting; however, inpatient visits will also be allowed if needed

^e^Wearable devices will be worn for one additional week after the end of the observation period (from Week 36), and symptoms are also recorded in the diary during this period; if the patient has discontinued, these recordings are terminated on the day of discontinuation

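### The primary AUC sums dose over days with no imputation and no rule for partial follow-up, so early leavers appear to be scored as levodopa-sparing, which favours whichever arm loses more patients

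*Protocol article*

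**What the plan says.** - **Endpoint (Efficacy outcomes):** the primary comparison is of "the cumulative additional dose of levodopa-containing medications during the treatment period (from Week 0 to Week 37").
- **Construction (Statistical methods):** the AUC "will be calculated as the total dose (daily dose × number of days) added to the dose of levodopa-containing medications" at randomization. Nothing divides the sum by time on study.
- **Missing data (Statistical methods):** "No imputation will be made for missing data".
- **End of observation (Table 1, footnote b, on the Week 36 column):** "Or the day immediately after discontinuation".
- **Completers (Statistical methods):** "For the secondary endpoints, the cumulative additional doses of levodopa will be calculated for the patients who completed the treatment (Week 37").
- **Analysis set (Statistical methods):** eligible patients are kept, "with the exception of those who withdraw consent before the start of the observation period (Week 0) or are withdrawn by the study investigator". Patients assigned to istradefylline who never start it are also excluded.
- **Titration (Study design, treatments, and blinding):** "if the clinical global impression of severity scale (CGI-S) is ≥ 4 on the day of observation, the dose is incrementally increased by 50 mg/day". Table 1 places the decision visits at Weeks 4, 8, …, 36.
- **Sample size (Statistical methods):** 111 patients, allowing for 10% drop-outs, to leave 50 per group evaluable for efficacy.

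**The concern.** An AUC built as dose × days has the same meaning for every patient only if every patient is observed over the same window. Here the window appears to close at discontinuation and nothing fills the remainder. The added dose rises in 50 mg/day steps, so much of a patient's AUC arises late. Leaving early removes the part that would have counted most.

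A low AUC is the favourable result. A patient who stops for intolerance, lack of benefit or any other reason is therefore ranked alongside patients who truly needed little extra levodopa. If the arms lose patients at different rates or times, the primary test partly compares retention rather than levodopa need.

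**Working it through.** **1. The plan's own figure.** 50 per group is 100 evaluable patients. 100 / (1 − 0.10) = 111.1, which agrees with the stated 111. This arithmetic gives drop-outs no evaluable data. The 80% power at a 21.3% difference cannot be reproduced, because the AUC distribution behind it is data on file.

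**2. What the rules imply together.** The efficacy set keeps patients who start and later stop, apart from investigator withdrawals whose timing is not given. The completers' AUC is a separate, secondary item. If non-completers were absent from the primary analysis, that item would repeat it. So non-completers are most naturally in the primary analysis. With a dose × days sum, a last assessment the day after discontinuation and no imputation, they carry a partial sum.

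**3. Effect on one patient.** One 50 mg/day step contributes 50 × 7 = 350 mg per week. AUC = 350 × Σ max(T − w, 0), over increase weeks w, with observation ending at week T.

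- Increases at Weeks 4, 12, 20, 28:
  - T = 37: 350 × (33 + 25 + 17 + 9) = 29,400 mg
  - T = 24: 350 × (20 + 12 + 4) = 12,600 mg (43%)
  - T = 12: 350 × 8 = 2,800 mg (10%)
- Increase at every decision visit: 53,550 mg at T = 37, 21,000 mg (39%) at T = 24, 4,200 mg (7.8%) at T = 12.
- One increase at Week 4: 11,550 mg at T = 37, 7,000 mg (61%) at T = 24, 2,800 mg (24%) at T = 12.
- Leaving before Week 4: 0 mg, the best possible score if no dose is reduced.

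**4. Effect on the test.** Simulation with no treatment effect: 55 per arm, nine decision visits, 50 mg steps, two-sided 5% Mann–Whitney test, 4,000 trials per setting. Assumptions not in the document: each patient's chance of an increase per visit is drawn from Beta(1, 1.5); dropout is unrelated to dose need; dropout by arm is as shown. The low end of each range has dropout spread over Weeks 0–37. The high end has it within about the first 12 weeks.

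| Dropout, istradefylline vs control | Rejection | Spurious AUC reduction |
|---|---|---|
| 10% vs 10% | about 5% | none |
| 12% vs 8% | 5–6% | small |
| 15% vs 5% | 7–12% | about 6–9% |
| 20% vs 5% | 10–19% | about 9–15% |

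The anticipated true effect is 20%.

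**5. The other direction.** With a true 30% cut in the chance of an increase, power is 52% without dropout. It falls to 19% if control loses 20% and istradefylline 5%, spread over the study.

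**6. Simple alternatives, at 20% vs 5% spread over the study.** Dividing by days observed still rejects in 9.2% of null trials, because the added dose grows with time. The completers' AUC rejects in 4.8%, but only because dropout was assumed unrelated to dose need.

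**The case against.** The strongest reply is that truncation is an inference. No sentence says the AUC stops at discontinuation, and the key link is a visit-schedule footnote. The sample-size text treats drop-outs as non-evaluable, and excluding patients withdrawn by the investigator may remove some early stoppers. A detailed analysis plan is promised before database lock. This stands as far as it goes. However, the summed AUC, the absence of imputation and the secondary place of the completers' AUC are fixed here, and an analysis plan that follows them inherits the problem. Reading drop-outs as non-evaluable conflicts with the analysis set and makes the completers' analysis redundant.

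A reader might infer that the type I error does exceed 5%. The document does not support that: equal dropout leaves it at about 5%, and a mild imbalance barely moves it. The larger figures need a three- or four-fold imbalance, and the 20% vs 5% case averages 12.5%, above the planned 10%.

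A reader might also infer that the bias favours istradefylline, since only that arm starts a new drug. That is plausible but not established. The trial is open-label and the drug is marketed in Japan for this indication, so control patients also have a reason to leave.

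The planned log-rank analysis and the by-visit dose comparisons do not sum over days and give some protection. They are secondary and do not repair the primary result.

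**Conclusion.** The concern holds in conditional form. Followed as written, the plan most naturally gives non-completers a truncated sum in the primary comparison, so early departure counts as levodopa sparing. The per-patient arithmetic depends only on the protocol's schedule and step size. The effect on the test depends on unequal dropout, for which the document gives no figures by arm or over time. It ranges from none at equal dropout to 7–12% false positives at 15% vs 5% and 10–19% at 20% vs 5%. The direction follows whichever arm loses more patients, and the result can equally be a loss of power. The exact sizes rest on the assumed escalation model and on dropout unrelated to need.

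This should be fixed before database lock. It is not proof that the trial's error rate is broken.

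**What to change.** 1. Define the primary AUC over the same Week 0–37 window for every patient in the efficacy set. State the estimand, including what discontinuation of study treatment means for it.
2. For this endpoint, replace the no-imputation rule with multiple imputation of the visit-level dose path after discontinuation, given arm, baseline CGI-S and the dose so far. State how the Mann–Whitney results are combined across imputations.
3. Add a sensitivity analysis that imputes istradefylline drop-outs from the control arm. Keep the truncated and completers' AUCs as sensitivity analyses only.
4. Reconcile the sample-size wording on evaluable patients with the analysis set, and say whether the investigator-withdrawal exclusion applies only before Week 0.
5. Where feasible, record the prescribed levodopa dose to Week 37 after study treatment stops.

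**Cost.** Items 1–4 need analysis-plan text and programming, with reliance on imputation assumptions for about 10% of patients. Item 5 is a modest addition to the Table 1 schedule, which does not show follow-up after discontinuation. Doses recorded then may reflect prescribing outside the protocol's titration rule, which is why the estimand must be stated first.

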There is considerable interest in a personalized approach to PD treatment [40–42], largely due to the clinical heterogeneity observed amongst patients. However, for this approach to be successful, there must be a clearer understanding of the associations between different subjective and objective measures of PD symptoms and the therapeutic outcomes. In this study, we intend to evaluate whether there is any relationship between the change in the index used to determine the dose increase of levodopa-containing medications (CGI-S) and the change in other indicators (CGI-I, PGI-I, PGI-S, CGI-S, mH&Y, MDS-UPDRS parts I–IV, PDQ-39, and data from the wearable device). The CGI was chosen as the criterion for increasing the levodopa dose as this reflects the routine clinical measure by which physicians judge dose adjustment; thus, by investigating the correlation between CGI and the other specified indicators, we can ascertain the objectivity of the CGI as a tool for therapeutic decision-making.

Finally, more severe dyskinesia is known to have a negative impact on patient quality of life (QOL) [43–45]. By identifying a therapy that reduces the levodopa dose and the risk of complications associated with levodopa-containing medications, studies such as this can contribute considerably to improving the QOL of PD patients and their families/caregivers. We believe that this study will provide a much-needed source of additional information, which can be used to underpin future treatment recommendations and practice to improve not only objective motor and non-motor symptoms, but also subjective and objective QOL, for the benefit of real-world PD patients.

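### Time to first levodopa increase is tested by a log-rank test that leaves out Week 0 CGI-S, although CGI-S triggers the event: valid, but probably inefficient

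*Protocol article*

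**What the plan says.** The Efficacy outcomes section lists "the number of days until the first dose increase after Week 4" among the secondary endpoints. The Statistical methods section fixes the comparison: "A log-rank test will be performed on the number of days from the start of observation (Week 0) to the time of dose increase", with Kaplan–Meier curves. It names no stratification or covariate for this or any other between-group test. The level is common to all comparisons: "A two-sided significance level of 5% will be applied to between-group comparisons". A detailed statistical analysis plan is promised before database lock.

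Three other places bear on the choice of test:

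- **Allocation** (Study design, treatments, and blinding). Patients go to "either the istradefylline group or the control group in a 1:1 ratio", "using a minimization method and stratified according to age" (cut at 60 years), levodopa equivalent dose (cut at 400 mg/day) and presence of dyskinesia.
- **The event** (same section, text after Table 1). The daily dose goes up by 50 mg "if the clinical global impression of severity scale (CGI-S) is" 4 or more on the day of observation. The Discussion confirms the link: "The CGI was chosen as the criterion for increasing the levodopa dose".
- **Baseline measurement** (Table 1). CGI-S is rated at Week 0, and dose-increase decisions run four-weekly from Week 4 to Week 36, which makes nine occasions. "CGI-S score and change in score" is itself a secondary endpoint, so the Week 0 value is needed in any case.

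**The concern.** The event is in essence the first post-baseline visit at which CGI-S reaches a threshold. Unless CGI-S is close to unrepeatable within a patient, its Week 0 value predicts how soon that happens. A log-rank test that ignores a strong predictor is pulled towards no difference, because the early events come mostly from patients who were already severe, in both arms. CGI-S is also not a minimisation factor, so with about 50 patients per arm a chance imbalance in it is handled neither by the design nor by the analysis.

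This endpoint speaks directly to whether istradefylline delays levodopa increases, which the Background offers as indirect evidence of levodopa sparing. What is at stake is power on one secondary comparison, not its validity.

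**Working it through.** **1. The plan's own figures.** The sample size is 100 evaluable patients inflated for 10% drop-out: 100 / 0.9 = 111.1. The article states 111 (rounding up gives 112). This figure, and the 80% power with 50 per group, belong to the Mann–Whitney test of the primary endpoint. For time to first increase the article gives no power, hazard ratio (HR) or event count. Everything below therefore rests on assumptions.

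**2. Rough scale for an unadjusted log-rank test.** Schoenfeld's approximation at 1:1 allocation is power = Φ(√d × |ln HR| / 2 − 1.96). With d = 60 events assumed:

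| HR | Power |
|---|---|
| 0.50 | 0.77 |
| 0.55 | 0.64 |
| 0.60 | 0.51 |
| 0.70 | 0.28 |

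For example, HR 0.55 gives √60 × 0.598 / 2 − 1.96 = 0.356, and Φ(0.356) = 0.64.

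**3. Simulation with prognostic strength set directly.** Inputs from the article: 100 patients, minimisation on three binary factors, events only at nine four-weekly visits, two-sided 5%. Assumed inputs: treatment HR 0.55 given the covariates, 45% of patients with Week 0 CGI-S of 4 or more, about 61 to 63 events. There were 1,000 runs per setting, with a Monte Carlo error of about ±3 points.

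*Stratifying by Week 0 CGI-S (below 4, or 4 and above):*

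| HR for CGI-S ≥ 4 | Unstratified | Stratified | Change (points) |
|---|---|---|---|
| 1 | 0.665 | 0.650 | −1.5 |
| 2 | 0.626 | 0.661 | +3.5 |
| 4 | 0.474 | 0.643 | +16.9 |
| 8 | 0.318 | 0.614 | +29.6 |

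In one mixed setting (CGI-S HR 4, each minimisation factor HR 1.5) the change was 0.471 to 0.595, or +12.4 points.

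*Stratifying by the eight minimisation cells:*

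| HR per factor | Unstratified | Stratified | Change (points) |
|---|---|---|---|
| 1 | 0.665 | 0.634 | −3.1 |
| 1.5 | 0.635 | 0.639 | +0.4 |
| 2 | 0.566 | 0.605 | +3.9 |

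With the factors not prognostic and CGI-S at HR 2, the eight cells lost 4.2 points (0.626 to 0.584).

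**4. Type I error.** With no treatment effect and prognostic minimisation factors (HR 1.5 to 2), the unstratified test rejected in 3.6 to 3.8% of runs and the eight-cell test in 4.9 to 6.0%. Across all null settings, the test stratified by CGI-S rejected in 3.7 to 6.0%. Nothing here suggests material inflation.

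**5. Simulation with the titration rule generating the event.** Here the prognostic strength follows from how repeatable CGI-S is within a patient (intraclass correlation, ICC). Assumed inputs: total SD 1, mean CGI-S 2.5, 3.0 or 3.5, a 0.5-point benefit, 10% drop-out. There were 50 patients per arm, an event at the first visit with CGI-S of 4 or more, and 500 runs per setting.

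| ICC | Log-rank | Cox (Efron) with Week 0 CGI-S | Cox gain (points) | Stratified log-rank gain (points) |
|---|---|---|---|---|
| 0.2 | 81–85% | 83–85% | 0–2 | 0–2 |
| 0.4 | 71–73% | 79–83% | 7–10 | 3–7 |
| 0.6 | 65–71% | 76–85% | 11–16 | 9–12 |
| 0.8 | 52–61% | 77–86% | 23–26 | 23–26 |

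Under no effect the Cox test rejected in 3 to 6% of runs. The two simulations agree in direction and rough size.

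**The case against.** The strongest reply is that nothing here is an error. A log-rank test is valid under randomisation with or without covariates, the endpoint is secondary, and strata or supportive models could still be set in the promised analysis plan. All of that stands. But the article does name a test, and using a baseline value that is already collected improves on that stated method; it does not fill in missing detail.

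Four stronger readings are tempting and should be set aside:

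- **That the trial throws away power it has been shown to have.** The stated 80% is for the primary endpoint; none is stated for this one.
- **That ignoring the minimisation factors is what costs power.** Their effect was about −4 to +4 points, close to simulation error, and eight strata in 100 patients can lose power.
- **That ties at nine visits undermine the planned test.** The log-rank variance allows for ties. Tie handling matters for a Cox model, not for the test as planned.
- **That Week 0 CGI-S is by construction the strongest predictor.** The rule uses CGI-S on the day, and the first decision is at Week 4. Strong prognosis is plausible, but the article gives no data on it.

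One objection limits the remedy. The trial is open-label. The analysis sets leave out patients who withdraw before Week 0 and those randomised to istradefylline who never start it, which suggests that allocation may come before the Week 0 visit. The article does not state the order. If allocation was known when CGI-S was rated, adjusting for that rating could bring in bias.

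**Conclusion.** The point holds as one of efficiency. The planned test is valid and, if anything, mildly conservative when prognostic factors are ignored. It probably gives up power because it leaves out the baseline value of the scale that triggers the event.

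The size depends on how prognostic Week 0 CGI-S is, which the documents do not say. The gain is about 0 to 3 points at an HR of 1 to 2 and about 17 to 30 points at an HR of 4 to 8. It is smaller (about 12 points) in the one setting where the minimisation factors were prognostic too. The loss is at most about 2 points if CGI-S carries no information. These figures assume a treatment HR of 0.55 or a 0.5-point CGI-S benefit and about 50 patients per arm. Because the possible gain is much larger than the possible loss, the change is worth making.

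**What to change.** Before database lock, prespecify the between-group test for time to first increase as one of these:

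- a log-rank test stratified by Week 0 CGI-S (below 4, or 4 and above); or
- a Cox model with Efron or exact ties, or a discrete-time complementary log-log model, with Week 0 CGI-S and the three minimisation factors as covariates, not as eight strata.

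Keep the Kaplan–Meier curves and the planned log-rank test as support.

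State when the Week 0 CGI-S is rated relative to allocation. If it is rated before allocation is known, use it in the main test. If not, adjust that test for the minimisation factors only and report the CGI-S-adjusted test as a sensitivity analysis.

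The cost is a few sentences of plan text and no new data. The model version adds a proportional-hazards assumption and estimates a conditional rather than a marginal effect. The choice has to be made in advance, because a covariate added after lock in an open-label trial would carry little credibility.
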